#### Data management and confidentiality

All electronic information will be password protected and stored on password protected computers in secure networks or on the TAP-App or REDCap software [36]. A coding system will be used to protect identifiable information. Only the Health TAPESTRY research team and volunteer coordinators will have access to the master file containing the coding system. Any electronic transfer of data will be done using a secure HTTPS protocol to mitigate risks associated with transferring information over the internet.

#### Data monitoring, critical and adverse events

Any critical incidents that volunteers encounter during study visits will be reported and followed up by the appropriate personnel using a standard operating procedure. Critical incidents include situations that prevent the visit from proceeding such as injury to a volunteer or client and emergency situations. Critical incidents identified by volunteers during the study will be immediately reported and monitored until the issue has been resolved.

Program-related adverse events from any source will be recorded. Adverse events are defined as “Any event that requires in-patient hospitalization or prolongation of existing hospitalization, causes congenital malformation, results in persistent or significant disability or incapacity, is life-threatening or results in death” [71]. The research team will monitor data conduct and oversee data quality and provide independent outcome adjudication of adverse events as potentially related to intervention or not, and to provide an assessment of the safety data at 6 months before the intervention is provided to the wait list control group.

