### Data collection

Outcome data collection will occur through the structured surveys via the TAP-App, from the electronic medical record (EMR), program records, and focus groups/interviews (Table 3). Health care utilization outcomes will be measured during the 6-month period prior to study enrollment (i.e., before baseline) and during the 6-month study period. For the EMR data extraction, all researchers will undergo training and use a standardized data abstraction form that has been pilot tested. We will calculate agreement scores between auditors for a subset of the sample.

**Table 3 Tab3:** Summary of outcomes, measures, and analysis plan using the RE-AIM framework

RE-AIM element	Outcome	Outcome measure; *source*	Data collection time point	Analysis
Reach *The reach of the intervention into the target population*	Participants	Proportion of eligible patients who consent; *self-report*	T_0_	Simple proportions and range across sites
	Sample characteristics	Demographics including chronic conditions; *self-report*, *EMR*	T_0_	Simple proportions and range across sites
	Volunteer visits	Number of volunteer visits; *program records*	T_6_	Frequency count across sites
Effectiveness *Positive and adverse effects of the intervention*	Hospitalizations*	Number of hospitalizations; *EMR*	T_0_, T_6_	Poisson regression or negative binomial regression
	Physical activity*	Total minutes spent doing moderate, vigorous, activity and walking (IPAQ); *self-report*;	T_0_, T_6_	Multiple linear regression
	Sitting	Hours sitting (IPAQ); *self-report*	T_0_, T_6_	
	Patient enablement	PEI; *self-report*	T_0_, T_6_	
	Quality of life	EQ 5D-5L; *self-report*	T_0_, T_6_	
	Treatment burden	MTBQ; *self-report*	T_0_, T_6_	
	Disease burden	DBMA; *self-report*	T_0_, T_6_	
	Emergency room or urgent care	Number of emergency room or urgent care visits; *EMR*	T_0_, T_6_	Poisson regression or negative binomial regression Poisson regression or negative binomial regression
	Falls	Number of falls; *EMR*	T_0_, T_6_	
	Medications	Number of medications; *EMR*	T_0_, T_6_	
	Primary care visits	Number of primary care visits; *EMR*	T_0_, T_6_	
	Negative effects	Unmet expectations; *self-report*	T_6_	Descriptive analysis across sites
		Labeling effect of screening tools; *self-report*	T_6_	
		Number and nature of serious adverse events; *EMR*	T_6_	

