### Data analysis

The results will be reported according to the CONSORT extension for pragmatic randomized trials [57] and non-pharmacological interventions [58]. The mean (standard deviation) or median (first quartile, third quartile) for continuous variables, depending on the distribution, and count (percent) for categorical variables will be calculated. The description of the data analysis approach below is separated based on the RE-AIM framework for effectiveness and implementation. Note that for reach, adoption, and maintenance, the analysis approach is found in Table 3.

Effectiveness: the effectiveness of Health TAPESTRY will be assessed at 6 months. We will adopt intention-to-treat (ITT) as the primary analysis approach. Multiple imputation approach using chained equations will be used to impute the missing data [59]. We will consider the fraction of missing information and determine the number of imputations needed using the two-stage approach suggested by Hippel [60]. The pooled effect estimates along with 95% confidence intervals will be reported. The co-primary outcome of a number of hospital admission will be analyzed using the Poisson regression or negative binomial regression depending on the distribution. The incidence rate ratio along with 95% confidence interval will be reported. And the co-primary outcome physical activity will be analyzed using the multiple linear regression. The mean difference between intervention and control group along with 95% confidence intervals will be reported. The continuous outcomes (sitting, patient enablement, quality of life, treatment and disease burden scores) and the count secondary outcomes (number of falls, number of primary care visits, number of emergency room or urgent care visits, number of medications) will be analyzed using the multiple linear and Poisson regression or negative binomial regression, respectively. The mean difference and incidence rate ratio along with 95% confidence intervals will be reported for continuous and count outcomes respectively.

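### The adverse-event rule filters on program-relatedness before relatedness is adjudicated and conflicts with Table 3, leaving deaths and total serious events without a stated comparison by arm

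*Protocol article*

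**What the plan says.** The section Data monitoring, critical and adverse events makes four statements that bear on this point.

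- Recording: "Program-related adverse events from any source will be recorded".
- Definition: "Any event that requires in-patient hospitalization or prolongation of existing hospitalization, causes congenital malformation, results in persistent or significant disability or incapacity", with life-threatening events and death completing the list. The definition does not mention relatedness.
- Adjudication: the research team is to "provide independent outcome adjudication of adverse events as potentially related to intervention or not".
- Review: the team is also to "provide an assessment of the safety data at 6 months before the intervention is provided to the wait list control group".

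Table 3, in the Data collection section, has a block for negative effects within the Effectiveness element. One row of it is "Number and nature of serious adverse events", sourced from the electronic medical record (EMR) at 6 months. The only analysis entry in that block is "Descriptive analysis across sites".

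The Data analysis section covers the outcomes to be compared between groups. For hospitalizations it says: "The co-primary outcome of a number of hospital admission will be analyzed using the Poisson regression or negative binomial regression depending on the distribution". The secondary counts compared by incidence rate ratio are "number of falls, number of primary care visits, number of emergency room or urgent care visits, number of medications". Treatment and disease burden scores are compared by mean difference. Serious adverse events and deaths are not among the outcomes named there.

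**The concern.** Relatedness cannot be both the condition for entering the record and the question decided afterwards. An event set aside at entry as unrelated never reaches the adjudicators. The article does not say who makes that first call or on what criteria, and the section Randomization and blinding states that those collecting outcome data are not blinded.

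The rule also works unequally in the two arms. An event in an intervention participant can be linked to a plan of care, a referral or a volunteer contact. An event in a control participant has almost nothing to be linked to before 6 months. A safety set built this way would hold mainly intervention events, and an excess in either arm could not be judged from it.

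Participants are 70 or older, so deaths within the study window are plausible. Death also ends the time during which a participant can be admitted. Without deaths by arm, the co-primary hospitalization result is harder to interpret. The Discussion says that risks need to be understood before the program is spread.

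**Working it through.** No figure in the plan has to be reproduced. The check sets the statements side by side.

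**1. Order of steps in the adverse-event section.** The definition depends on seriousness only. The recording rule adds relatedness. The adjudication step then divides adverse events into potentially related or not. If recording follows the rule literally, the adjudicators see only events that someone has already called related. If they are to see unrelated events too, the recording rule is worded wrongly. Both cannot hold as written.

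**2. What the rule captures in each arm.**

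- Intervention (section Intervention group): report to the huddle, plan of care, possible volunteer help, and survey visits. Many routes exist by which an event could be called program-related.
- Control (sections Procedures and data collection, and Control group): volunteer survey visits at the start and at 6 months, but no report, huddle or volunteer follow-up in between. Only an event arising from a survey visit could plausibly qualify. The expected control contribution is close to none, though not exactly none.

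**3. Adverse-event section against Table 3.**

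- Case definition: the section restricts to program-related events; Table 3 does not restrict.
- Source: the section accepts any source; Table 3 names the EMR.
- Analysis: the section promises a 6-month safety assessment without naming a comparison; Table 3 gives a description across sites. That entry is printed against the first row of the negative-effects block, and the serious-event row has none of its own. I read it as applying to the whole block.

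The two places therefore describe different sets of events for what appears to be the same outcome. This affects what is abstracted from the chart, so a later analysis plan could not settle it by choice of analysis alone.

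**4. Which components of harm are compared by arm.**

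- In-patient hospitalization: yes, as a co-primary outcome.
- Falls, and emergency or urgent care visits: yes, as secondary counts.
- Treatment burden and disease burden: yes, as secondary scores.
- Death: no comparison stated. In the article it appears only within the adverse-event definition.
- Life-threatening events, and persistent or significant disability: no comparison stated.
- Total number of serious events, or participants with at least one: no comparison stated.

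**The case against.** The strongest reply is that the plan already compares harm by arm on several outcomes. This stands. A reader might infer from the adverse-event section that the trial yields no between-arm safety comparison at all. The documents do not support that, because hospitalizations, falls, emergency or urgent care visits and both burden scores are analysed between groups.

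A reader might also reason that every control admission meets the adverse-event definition and would be lost under the filter. That does not follow either. Admissions in both arms are taken from the chart audit, classified by reason, and compared as a co-primary outcome.

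Three further replies have some force.

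- The recording sentence does not say that only program-related events are recorded, and Table 3 lists serious events without the filter. I accept that exclusive recording is not established. What remains is that two sections give different rules, and the one written as the recording rule is the narrower.
- The adverse-event section could describe two stages, with suspected program-related events logged and then adjudicated. This softens the circularity but does not help the control arm, where there is almost nothing to suspect.
- Describing results across sites does not rule out tabulating them by arm, and a full protocol or analysis plan may do so. I accept this, so the absence of a by-arm table is not the main point. The main point is a stated capture rule that, if followed, would give a one-sided set to tabulate.

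The Discussion's claim that assessing negative outcomes is a strength names disease burden, treatment burden and labelling effects. The first two are compared by arm, so that claim is not contradicted.

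**Conclusion.** The point holds in a limited form. The adverse-event section conditions recording on relatedness, defines the event without it, and adjudicates it afterwards. It also conflicts with the unrestricted serious-event row in Table 3. Followed as written, it would leave almost no recorded adverse events in the control arm, and the 6-month safety assessment would have almost no concurrent control data if it drew on that record.

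The consequence is confined to deaths, life-threatening events, disability and the total serious-event count. The article gives no expected rates for any of these, so I put no number on the gap.

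The conclusion rests on two assumptions: that the recording sentence is applied literally, and that the single analysis entry in the negative-effects block covers the serious-event row. If the second is wrong, that row has no analysis stated in the table, and the conflict over what is recorded is unchanged. The matter should be corrected, but it does not threaten the primary comparison.

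**What to change.** Reconcile the adverse-event section with Table 3:

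1. Remove the program-related condition from the recording sentence. State that all events meeting the given definition, deaths included, are recorded in both arms over the same 6 months from the EMR audit.
2. Adjudicate relatedness after recording and keep it as an attribute of each event, not as a condition of entry.
3. In Table 3, give the serious-event row its own analysis entry: number of events and number of participants with at least one event, by arm as well as by site, with deaths shown separately. A descriptive table is enough.
4. State that the 6-month safety assessment uses this set.

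The cost is a change of wording, a small addition to the abstraction form, and one more table. Charts in both arms are already to be audited for hospitalizations over the same window, so no new data source or participant contact is needed. Incomplete charts, which the Discussion already acknowledges, will limit this outcome as they limit the others.

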## Methods/design

### Trial design

This study is a pragmatic parallel randomized controlled trial with a delayed intervention for control participants at 6 months. We will simultaneously assess effectiveness and implementation strategy in a real-world setting (type II hybrid) [32]. The main group comparisons will be at 6 months. We report this study protocol in accordance with the SPIRIT guidelines (see Additional file 1 for the checklist; see Fig. 1 for the SPIRIT Figure) [33] and TIDier checklist (see Additional file 2) [34]. We will use mixed-methods data collection, mapping onto the adoption, implementation, and maintenance domains in RE-AIM.

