### Intervention

#### Procedures and data collection

A participant (termed “client” within the program), regardless of allocation, will receive a visit in their home from two volunteers at the start of the study and again 6 months later. The volunteers will collect data using structured surveys on the Health TAPESTRY web-based application (TAP-App) covering a variety of domains (i.e., physical activity, nutrition, mobility, quality of life; see Table 2). The volunteers will enter all data into the TAP-App using a tablet computer. The volunteers may return to the client’s home multiple times until all the surveys are complete. Participants may withdraw from the study at any point by informing the volunteer coordinator.

**Table 2 Tab2:** List of all TAP-App surveys

Construct *Survey name*	Survey description	Key information for TAP-Report	Intervention		Control	
			T_**0**_	T_**6**_	T_**0**_	T_**6**_
Demographic information *Custom*	Basic demographics	NA	X		X	
Quality of life* *EQ 5D-5L* [37]	Quality of life with respect to mobility, self-care, usual activities, pain, and anxiety/depression. Five answer options provided from able to/none to extremely difficult/extreme levels (scores ranges 0–1, higher scores = higher quality of life)	• Severe problems in walking about or unable to walk about • Severe problems washing or dressing self or unable to wash or dress self • Severe problems doing usual activities or unable to do usual activities • Severe pain/discomfort or extreme pain/discomfort • Severely anxious/depressed or extremely anxious/depressed	X	X	X	X
Physical activity *I**nternational Physical Activity Questionnaire (IPAQ)* *(short)* [38]*	Time spent doing physical activity per week	Calculated time in moderate and vigorous physical activity Time spent sitting in one typical day (in hours)	X	X	X	X
*Rapid Assessment of Physical Activity (RAPA)* [39]	Quick assessment of physical activity for older adults (score range 1–7, higher scores = higher physical activity)	Suboptimal physical activity (score < 6)	X	X	X	X
Enablement* *Patient Enablement Instrument (PEI)* [40]	Client’s ability to cope with, or have Control over their health after visit with health care team	NA	X	X	X	X
Treatment burden* *Multimorbidity Treatment Burden Questionnaire (MTBQ)* [41]	Level of difficulty of 10 treatment tasks (e.g., taking many medications)	NA	X	X	X	X

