#### Control group

Once the baseline visit is complete, control clients will receive usual care. No report will go to the TAP-Huddle until the client received the intervention, nor will any volunteer follow-up take place. After, 6-month research outcomes are collected, and clients will be offered the Health TAPESTRY program.

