### Trial status and dissemination policy

This trial is in the recruitment phase, and we expect the final 6-month follow-up visit for the intervention and control participants to occur in mid-2020. Recruitment began on March 15, 2018, and is expected to conclude at the end of January 2020. The study is using protocol version 2, dated July 2018. The results of this study will be published in peer-reviewed academic journals and presented at academic conferences. The datasets analyzed during the current study will be available from the corresponding author on reasonable request.

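### An assessment of complete 6-month safety data cannot precede the first controls' move to the program, because controls appear to cross over on their own 6-month clocks

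*Protocol article*

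**What the plan says.** The safeguard is in the protocol article under Data monitoring, critical and adverse events. The research team is to adjudicate whether adverse events relate to the intervention and to provide "an assessment of the safety data at 6 months before the intervention is provided to the wait list control group". The same section says "Program-related adverse events from any source will be recorded" and has critical incidents at visits reported at once and followed up.

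The timing of crossover is given elsewhere:

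- Trial design describes a "pragmatic parallel randomized controlled trial with a delayed intervention for control participants at 6 months".
- Procedures and data collection says that every participant, whatever the allocation, "will receive a visit in their home from two volunteers at the start of the study and again 6 months later".
- Control group says "After, 6-month research outcomes are collected, and clients will be offered the Health TAPESTRY program".
- In Table 2, controls first complete several program surveys (goals, daily activities, frailty and nutrition among them) at T6, not at baseline.

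The calendar is under Trial status and dissemination policy: "Recruitment began on March 15, 2018, and is expected to conclude at the end of January 2020", and "we expect the final 6-month follow-up visit for the intervention and control participants to occur in mid-2020".

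**The concern.** The safeguard is worded as a single step: 6-month safety data are assessed, and then the control group receives the program. That order works if all controls cross over together after follow-up closes. It does not work if each control crosses over six months after entering a trial that recruits for nearly two years.

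The stake is the credibility of a stated patient-safety check. Participants are aged 70 or older, and the adverse events defined in that section include hospitalization, life-threatening events and death. A reader or an ethics board would take the sentence to mean that evidence on the program's safety exists before controls are exposed to it. For the earliest controls there would be almost none from completed follow-up.

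**Working it through.** **Inputs.** Recruitment opens 15 March 2018 and closes at the end of January 2020 (Trial status). The control delay is 6 months (Trial design). The planned sample is 586, allocated 1:1 (Sample size; Randomization and blinding), so about 293 per arm. Uniform accrual and a baseline visit soon after enrolment are my assumptions.

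**The plan's own date.** End of January 2020 + 6 months = end of July 2020. This agrees with the stated mid-2020 for the final 6-month visit.

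**First control due.** 15 March 2018 + 6 months = 15 September 2018. This is the earliest possible date, since it assumes a control is enrolled and visited as soon as recruitment opens.

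**Gap between first crossover and complete data.** 15 September 2018 to 31 July 2020 = 685 days; 685 / 30.44 = 22.5 months.

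**Data available when the first control falls due.** Recruitment lasts 687 days, of which 184 have passed by 15 September 2018. 184 / 687 = 27%, or about 157 of 586 enrolled. Only those enrolled at the very start have six months of follow-up, so the completed share is close to zero.

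**Data available later.** Controls and intervention participants share the same 6-month clock. A control enrolled when a fraction *u* of recruitment has elapsed therefore falls due when about a fraction *u* of the intervention arm has completed six months. For the median control, *u* = 0.5, so about 0.5 × 293 ≈ 147 intervention participants are complete. On the calendar, the median control is enrolled about 343 days in (late February 2019) and is due in late August 2019.

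**Could all controls wait?** Holding every control until the last 6-month visit would delay the first one by 184 + 685 = 869 days, or 869 / 30.44 = 28.5 months. That contradicts the 6-month delay in Trial design.

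**Could it be a check on each control's own data?** A control's first six months contain usual care and no program delivery, so they cannot inform program safety.

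**When the data arrive.** Table 3 lists serious adverse events as a chart-derived measure at T6, and the Discussion calls chart audit laborious. Complete data would come somewhat after the visit dates used above.

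**The case against.** The strongest reply is that the sentence does not say the assessment is single, trial-wide or based on complete data. The team could review the intervention-arm data accrued by the time each control falls due. A staggered design can supply that, and the evidence would grow from almost nothing to nearly the whole arm. This stands. A reader might infer that no safety assessment can ever precede crossover, and the document does not support that. What fails is the reading the words most naturally carry: one assessment of the 6-month data before the group is exposed. The cumulative reading is feasible, but it is not stated.

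Several further points also stand:

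- Staggered crossover is an inference, though a strong one. The Control group section gives no interval and does not expressly exclude a hold.
- A reader might conclude that accumulating safety goes unwatched. The document does not say that: besides incident reporting and adjudication, Strategies to improve adherence to protocol provides bi-weekly team meetings. What is not stated is a scheduled aggregate review.
- Under uniform accrual, (687 − 184) / 687 = 73% of controls fall due before recruitment closes. A reader might take that as the size of the problem, but it does not show how much intervention-arm evidence exists when a control falls due.
- The 6-month comparison precedes crossover, so no primary estimate or error rate changes.

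It can also be said that cut-offs belong in the full protocol, which is not shown. That excuses missing detail. It does not excuse a stated safeguard whose timing conflicts with other sections of the same article.

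**Conclusion.** The point holds in a limited form. An assessment of complete 6-month safety data cannot come before the first controls are offered the program, because those data are complete only about 22.5 months after the earliest crossover date. The first controls would cross over with almost no completed intervention follow-up behind them, and the median control with about half the intervention arm complete.

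The conflict rests on the document's dates and on crossover following each participant's own 6-month visit, which Trial design, Procedures, Control group and Table 2 all indicate. The one-half figure rests on uniform accrual, and mid-September 2018 on prompt first visits. The consequence is an overstated safeguard, with no bias in the effectiveness analysis.

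**What to change.** Reconcile Data monitoring, critical and adverse events with Control group and Trial status. Either of two changes would do:

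1. Restate the safeguard as a cumulative review of the program-related adverse events already recorded in intervention participants, at stated calendar cut-offs.
2. Withdraw the claim that an assessment of 6-month safety data precedes crossover, and describe only the incident reporting and adjudication that the design does provide.

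The cost is a change of wording and, under the first option, a little periodic tabulation of events already being recorded. No extra participants are needed. The review should stay with program-related events. Hospitalization is both part of the adverse event definition and a co-primary outcome, and those collecting outcome data are not blinded, so a periodic by-arm table of all serious events would be an interim look at that outcome. It could also require chart audits ahead of schedule.

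Which crossover rule applies is for the investigators; the document needs only to state it consistently.
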